## Abstract

**Background:**

Atypical sensory reactivity is a cardinal presentation in autism. Within the tactile domain, atypical tactile reactivity (TR) is common, it emerges early, persists into adulthood, and impedes social interaction and daily functioning. Hence, atypical TR is a key target for biological intervention to improve outcomes. Brain mechanisms informing biological interventions for atypical TR remains elusive. We previously reported hyper-plasticity in the motor cortex in autistic adults and found that repetitive transcranial magnetic stimulation (rTMS), designed to strengthen inhibitory processes in the brain, reduced hyper-plasticity. Whether the primary sensory cortex (S1) is characterized by hyper-plasticity, which may underlie atypical TR in autism is unknown.

**Objectives:**

We aim to test whether hyper-plasticity in the S1 underlies atypical TR in autism, and investigate if a single session of rTMS can safely reduce hyper-plasticity in S1 in autistic adults.

**Method:**

Plasticity will be assessed in the left S1 with integrated paired associative stimulation and electroencephalography (PAS-EEG) paradigm in 32 autistic adults and 32 age-, sex-, and intelligence quotient-matched controls. Autistic participants will be further randomized (double-blind, 1:1) to receive a single-session of either sham or active 20 Hz bilateral rTMS over the S1 and the plasticity will be re-assessed over the left S1 on the same day.

**Conclusions:**

Atypical TR has been identified as one of the top clinical research priorities that can influence outcome in autistic population. The study findings can be highly valuable to further elucidate the mechanism underlying atypical TR, which in turn can help with developing a mechanism-driven intervention.

## Introduction

Autism Spectrum Disorder (hereafter will be called autism) is one of the most common neurodevelopmental conditions, affecting approximately 1% of the world population [1]. It is estimated that over 90% of autistic individuals exhibit atypical sensory reactivity [2]. Atypical sensory reactivity in the form of hyper- or hypo-reactivity to external stimuli is a cardinal presentation in autism. In the sensory domain, atypical tactile reactivity (TR) is a common presentation that emerges early, persists into adulthood, and adversely affects social interaction and daily functioning, thus significantly contributing to the overall disability [3,4]. An international commission on the future of care and clinical research in autism identified the sensory domain as one of the top clinical research priorities that can influence care and outcome in autism [5]. We engaged autistic adults attending our specialized autism clinic and received consistent feedback that this is a high-priority area of significant unmet need. Behaviorally, both tactile hypo- and hyper-reactivity are believed to be on the same continuum reflecting the same underlying biological process where hypo-reactivity is a coping mechanism to deal with excessive stimulation [6]. Neurophysiologic studies of tactile processing [4,6] and neuroimaging studies of excitatory and inhibitory metabolites in the primary sensory cortex (S1) in autism remain inconsistent and inconclusive [7,8]; therefore, brain processes informing biological interventions for atypical TR remains elusive.

Converging evidence indicates that the neurobiology of autism is characterized by atypical plasticity. A key insight from well-characterized valproic acid animal models of autism is that an excessive long-term potentiation (LTP) plasticity or hyper-plasticity adversely affects behavior [9–11]. Hyper-plasticity was found in the S1 of mice that displayed atypical TR [11]. Whether the S1 is characterized by hyper-plasticity, which may underlie atypical TR in autistic humans, is unknown.

A more direct evidence of hyper-plasticity was consistently observed in human motor cortex using transcranial magnetic stimulation (TMS) [12–15] with one exception [16]. Our group replicated this finding of hyper-plasticity in the motor cortex in autistic adults [15]. As a foundation for intervention, we also collected pilot data using a repetitive transcranial magnetic stimulation (rTMS) protocol designed to strengthen inhibitory mechanisms, which reduced hyper-plasticity in autistic adults [15]. In our previously published study [15], we conducted a randomized trial involving 29 autistic adults. The participants were allocated (1:1) to undergo either a single session of active or sham rTMS, with 6,000 pulses applied at 20Hz, targeting the motor cortex. The results revealed a substantial effect size of active rTMS on Long-Term Potentiation (LTP), with LTP reduction observed on the day following rTMS. This decrease in hyper-plasticity aligns with the altered neuronal excitation/inhibition (E/I) model of autism [17]. According to this model, the hyper-plasticity observed in autism is associated with an increased E/I ratio, and facilitating inhibition could contribute to the observed reduction. The rationale for using 20 Hz rTMS is primarily based on our group’s previous studies, which demonstrated that, contrary to earlier conventions, frequency alone does not determine the excitatory or inhibitory effects of rTMS. Instead, the ‘dose,’ or the number of stimulation pulses, is also a critical factor [18,19]. Daskalakis et al. reported that 20 Hz rTMS, when delivered in 900 pulses, significantly prolonged the cortical silent period (CSP), an index of GABA-B-mediated inhibition, compared to the widely-used 1 Hz inhibitory protocol and the 10 Hz rTMS protocol [18]. De Jesus et al. further supported these findings and showed that CSP prolongation could be maximized when 20 Hz rTMS was delivered in 6,000 pulses [19]. Additional details regarding the rationale behind this approach has been previously published by our team [20].

Our primary goal is to test whether the S1 hyper-plasticity underlies atypical TR in autism. In this study, we will use the innovative combination of paired associative stimulation (PAS), a well-established TMS paradigm to study plasticity, and electroencephalography (EEG) or PAS-EEG, to assess plasticity [21]. In PAS-EEG experiment, PAS induced LTP-like (i.e. PAS-LTP-like) is defined by potentiation of cortical evoked activity (CEA), which is measured by EEG. The reproducibility of the PAS-EEG method was reported in independent samples [22,23]. We will also explore if a single session of ‘mechanism-driven’ rTMS [15] described above can reduce hyper-plasticity in the S1 and whether it is well-tolerated by autistic adults.

## Objectives

In this study, there are four objectives:

(**1**) To assess and compare plasticity in the S1 between autistic adults and neurotypical controls.(**2**) To examine the relationship between TR and plasticity in the S1 within both study groups, i.e. autistic and neurotypical.(**3**) To investigate if a single-session of active bilateral rTMS delivered to the S1 can reduce the S1 hyper-plasticity in autistic adults.(**4**) To assess tolerability of bilateral rTMS to the S1.

## Hypotheses

Our hypotheses are as follows:

Hypothesis 1: Compared to neurotypical controls, autistic adults will display hyper-plasticity (i.e. significantly greater LTP-like plasticity) in the S1.Hypothesis 2: There will be a positive association between plasticity and TR, however, the association will only be significant for the autistic group reflecting hyper-plasticity underlying excessive TR.Hypothesis 3: Autistic adults randomized to active bilateral rTMS will have less LTP-like plasticity in S1 following a single session of active rTMS than those randomized to single session of sham bilateral rTMS.Hypothesis 4: Bilateral active rTMS to S1 will be well-tolerated.

## Method

### Design and setting

The current study, comprising two phases (Fig 1), one of which is randomized and double-blind, will be conducted at CAMH’s Temerty Centre for Therapeutic Brain Intervention, Toronto, Canada, from April 2023 to April 2025. The authors assert that all procedures contributing to this work comply with the ethical standards of the relevant national and institutional committees on human experimentation and with the Helsinki Declaration of 1975, as revised in 2013. All procedures involving human subjects were reviewed and approved by the research ethics board at CAMH (135/2019).

**Fig 1 pone.0305013.g001:**
[figure not shown]
Schematic diagram of the study design. Initially, all participants (*N* = 64) will undergo a baseline clinical assessment and MRI brain scan. In their third visit, the participants will complete the SPQ questionnaire and the plasticity in the left S1 will be assessed using PAS-EEG. Only autistic participants will be further randomly assigned to either the active or sham group, in a double-blind manner, to receive bilateral rTMS over the S1, and the plasticity of the left S1 will be reassessed on the same day following rTMS. This session will be scheduled at least one week after the third visit. WASI-II, Wechsler Abbreviate Scale for intelligence—second edition; EHI, Edinberg Handedness Inventory; Edinberg Handedness Inventory (ARBQ-2); Social Responsiveness Scale-2 (SRS-2); Ritvo Autism Diagnostic Scale-Revised (RAADS-R); Autism Diagnostic Observation Schedule—second edition (ADOS-2); MRI: Magnetic resonance imaging; SPQ: Sensory Perception Quotient; PAS: Paired associative stimulation; EEG: Electroencephalography; S1: Primary sensory cortex; rTMS: Repetitive transcranial magnetic stimulation.

All participants, both autistic and neurotypical, will undergo clinical assessments, which include diagnosis confirmation, handedness determination, IQ evaluation, and a TMS safety screen. Additionally, they will undergo a magnetic resonance imaging (MRI) scan of the brain, which will be used for MRI-guided neuronavigated TMS in subsequent sessions. On their next visit, all participants will complete the 92-item Sensory perception Quotient to assess TR [24]. Then, plasticity will be assessed in the left S1 using PAS-EEG paradigm.

Upon completing the first phase, only autistic participants will be randomly assigned in a double-blind manner (1:1) to receive either a single-session of active or sham bilateral rTMS over the S1, followed by PAS-EEG plasticity assessment session, on the same day. Assignment will be determined using a permuted block randomization method [25] generated by an independent biostatistician external to the project. The participants and investigators involved in the study will remain blinded throughout the study, i.e. experiment and data analysis. The investigators will be unblinded only after the analysis of data is completed.

The rTMS session will be scheduled with at least a one-week gap from the first plasticity assessment session to allow any potential carryover effects from the PAS to dissipate. This ensures that the subsequent rTMS treatment will not be influenced by the prior PAS intervention. The first participant was recruited on June 08, 2023. Fig 1 provides a schematic diagram illustrating the study design.

### Participants

This study aims to enroll a total of 64 participants, comprising 32 adults diagnosed with autism as per fifth edition of the Diagnostic and Statistical Manual of Mental Disorders (DSM-5), without intellectual disability [26]. This diagnosis will be confirmed through clinical assessment and the Autism Diagnostic Observation Schedule-2 (ADOS-2) [27].

It is important to note that our study will encompass autistic participants who have stable co-occurring mental health conditions and medications [28]. Research findings indicate that 70% of young autistic individuals have at least one co-occurring mental health condition [29–31], and almost half of them meet criteria for more than one [30,31]. We believe that excluding individuals with co-occurring mental health conditions and medication use is impractical and would hinder the generalizability of our findings. In addition, given the normative sex differences in plasticity [32], we will recruit at least 11 females, reflecting a higher male:female (2:1) ratio compared to previous ratio of 2.5–3:1 [33].

Autistic participants will primarily be recruited from Adult Neurodevelopmental Services outpatient clinics at CAMH, and CAMH research registry.

For the control group, an additional 32 neurotypical participants will be recruited through the healthy control registry, alongside advertising at local universities and in newspapers. The recruitment process will involve a 1:1 matching strategy, ensuring that for each autistic adult, a corresponding neurotypical counterpart will be sought based on age, sex, and IQ.

All prospective participants, expressing their willingness to take part in this study, will be referred to our research analyst for a detailed discussion about the study’s objectives, protocols, potential risks, and their rights as research participants. Our research team will then assess the participant’s eligibility for inclusion in the study, with the inclusion and exclusion criteria detailed in Table 1. Each participant will be required to provide a written consent at the outset of the study.

**Table 1 pone.0305013.t001:** Inclusion and exclusion criteria.

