**Outcomes**
*Primary Outcome*. The primary outcome measure of this study is the PAS-induced LTP-like plasticity in the S1. PAS-induced LTP-like plasticity will be assessed using CEA. CEA is quantified as the area under the curve of rectified TMS-EEG response within a time window of 25–275 ms from TMS stimulus onset [44]. This chosen time window is designed to exclude any early artifacts and account for the subsiding effects of TMS. CEA will be averaged across 100 epochs from the electrodes of interest corresponding to the S1 region. The mean post-PAS CEA will be then divided by the pre-PAS CEA, reflecting the potentiation of CEA at each of post-PAS time points (0, 15, 30, and 60 minutes). Given that the timing of the post-PAS maximum potentiation could differ among participants, we will use the maximum CEA ratio for each participant for the statistical analysis [21].

To asses TR, the total score on the “touch” category of SPQ questionnaire will be used.

**A *Priori* power calculation** A sample size of *N* = 64 participants, consisting of 32 autistic participants and 32 neurotypical controls, has been determined as adequate for hypothesis testing. This sample size provides 90% power. This calculation is based on the preliminary data, the observed LTP-like plasticity difference of 20.6 points [15], as evidenced in our PAS-EEG pilot study involving both autistic adults and control subjects. Moreover, the same sample size is deemed suitable for evaluating hypotheses 2, offering an 80% statistical power to detect a moderate effect size (Cohen’s f2 = 0.15). These power calculations were executed using G*Power [45].

Drawing upon our previously published findings [15], we envision a "substantial" impact of active rTMS in a group of 16 autistic participants when compared to a sham group also consisting of 16 autistic participants. It is important to note that, given the relatively small sample size, the application of a single session, and the exploratory nature of this outcome, our approach to presenting results and their interpretation will extend beyond statistical significance values. Instead, we will place significant emphasis on estimated effects and their precision, including the calculation of 95% confidence intervals. This comprehensive set of information, combined with data related to tolerability, will play a pivotal role in shaping the design of future clinical trials.

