#### Statistical analysis

Hypothesis 1: To test this hypothesis, we will employ a linear regression model with CEA ratio (LTP-like plasticity) as dependent variable and study groups (autistic and neurotypical controls) as independent variable. Age, sex, hemisphere of PAS-EEG assessment, IQ and pre-PAS CEA (an index of individual baseline cortical excitability) will enter the model as ‘control’ independent variables. To ensure robustness, a model diagnostic will be conducted through visual inspection of model residuals for lack of normality, heteroscedasticity, linearity and outliers [46] and Cook’s distance [47] will be used to inspect for influential data points. Potential confounding effect of medication use among autistic adults on plasticity will be investigated in a post-hoc sensitivity analysis that will include mediation as an additional control.

Hypothesis 2: We will use a multivariate analysis of variance to test this hypothesis where TR, as dependent variable, is associated with plasticity in the autism group; S1 plasticity, study groups and their interaction will be the main predictors; and sex, age, hemisphere of PAS-EEG assessment and IQ will enter the model as controls. If the interaction between S1 plasticity and study group proves to be significant at confidence level 0.05, the model estimated slopes of S1 within each group will be investigate using graphs.

Hypotheses 3 & 4: In order to study the effect of active vs. sham rTMS on LTP-like plasticity, we will use an analysis of covariance with CEA ratio (LTP-like plasticity) as dependent variable, groups (active and sham rTMS) as fixed factor, and pre-rTMS CEA ratio as covariate. We will count discontinuation of rTMS session and adverse events to assess tolerability.

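### The protocol names sex as related to plasticity and adjusts Hypotheses 1 and 2 for it, but the stated Hypothesis 3 ANCOVA (16 v 16) leaves sex out

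*Protocol article*

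**What the plan says.** The Participants section of the protocol article plans a sample "comprising 32 adults diagnosed with autism". It ties the sex composition to the outcome: "given the normative sex differences in plasticity [32], we will recruit at least 11 females". The quota corresponds to a 2:1 male:female ratio. Controls are matched one to one on age, sex and IQ.

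Under Statistical analysis, the control variables for Hypothesis 1 are "Age, sex, hemisphere of PAS-EEG assessment, IQ and pre-PAS CEA". The Hypothesis 2 model also lists sex, with age, hemisphere and IQ. For Hypothesis 3 the dependent variable is again the CEA ratio, and the model contains "groups (active and sham rTMS) as fixed factor, and pre-rTMS CEA ratio as covariate". Sex is not listed.

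On allocation, Design and setting states: "Assignment will be determined using a permuted block randomization method [25] generated by an independent biostatistician external to the project". It names no stratification factor and does not say that there is none. Under the power calculation, the comparison is "active rTMS in a group of 16 autistic participants when compared to a sham group also consisting of 16 autistic participants". That section calls the outcome exploratory and says interpretation will rest on estimated effects and 95% confidence intervals, which are to inform later trials.

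**The concern.** The document treats sex as related to plasticity in its quota, its matching and two of its three models. It then drops sex from the third, which has the same outcome and the fewest participants. No reason is given. The Hypothesis 1 groups are already matched on sex and are still adjusted for it, while the article describes no sex balancing for the two rTMS arms.

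With 16 per arm, chance can place clearly more females in one arm. If sex predicts the post-rTMS CEA ratio beyond what the pre-rTMS ratio captures, part of that imbalance appears in the active-sham difference. Because this estimate and its interval are meant to shape future trials, how close the single realised value lies to the truth matters even though no confirmatory test depends on it.

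**Working it through.** **Inputs from the article.** 32 autistic adults; at least 11 females; 2:1 male:female ratio; 1:1 allocation; 16 per arm; Hypothesis 3 model with arm and pre-rTMS CEA ratio.

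**Assumptions not in the article.** Allocation unstratified by sex; a sex effect d of 0.5 to 0.8 SD of the CEA ratio, equal before and after rTMS; a pre/post correlation ρ of 0.3 to 0.6 (0.7 is also shown in step 3).

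1. *The plan's own figure.* One third of 32 is 10.67, rounded up to 11. The quota reproduces and refers to the 32 autistic adults.

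2. *Chance of imbalance.* With 11 females among 32 and 16 drawn for one arm, P(x females) = C(11,x)·C(21,16−x)/C(32,16), where C(32,16) = 601,080,390.
   - 8 v 3 or worse, either direction: 2 × (33,575,850 + 6,395,400 + 596,904 + 20,349)/601,080,390 = 0.135.
   - 7 v 4 or worse: add 96,996,900 inside the bracket, giving 2 × 137,585,403/601,080,390 = 0.458.
   - 9 v 2 or worse: 2 × 7,012,653/601,080,390 = 0.023.
   - Eleven is a minimum. With 12 females, a difference of 5 or more has probability 6.6%; with 16 females, 7.6%.

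3. *Approximate shift at 8 v 3.* Shift ≈ (5/16) × d × (1 − ρ). With d = 0.5 and no baseline adjustment: 0.3125 × 0.5 = 0.16 SD. With the planned covariate: 0.16 × 0.7 = 0.11 SD at ρ = 0.3; 0.16 × 0.5 = 0.08 at ρ = 0.5; 0.16 × 0.3 = 0.05 at ρ = 0.7.

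4. *Simulation.* 8,000 trials per scenario, 11 females, unstratified permuted blocks of 4 (block size assumed), no treatment effect, ANCOVA with and without sex. The shift columns give the mean shift, in SD, towards the arm with more females, among trials whose arms differ by 5 or more females. The SD columns cover all trials.

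| d | ρ | Shift, planned model | Shift, sex added | SD of estimate, planned | SD of estimate, sex added |
|---|---|---|---|---|---|
| 0 | 0.3 | −0.011 | −0.006 | 0.350 | 0.355 |
| 0 | 0.6 | −0.009 | −0.010 | 0.288 | 0.293 |
| 0.5 | 0.3 | 0.117 | 0.000 | 0.347 | 0.347 |
| 0.5 | 0.6 | 0.057 | 0.001 | 0.292 | 0.295 |
| 0.8 | 0.3 | 0.167 | 0.008 | 0.356 | 0.351 |
| 0.8 | 0.6 | 0.088 | −0.009 | 0.296 | 0.298 |

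   Relative to the standard error, the planned model's shift runs from 0.057/0.292 = 0.2 to 0.167/0.356 = 0.5. Over all randomisations both models average within 0.01 SD of zero. Type I error is 4.6% to 5.4% across the six scenarios.

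5. *Cost of the covariate.* Residual degrees of freedom: 32 − 3 = 29 as planned, 32 − 4 = 28 with sex. If sex has no effect, the SD of the estimate rises by about 1.5% (0.2926/0.2883 = 1.015).

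6. *Scale.* An unadjusted two-sided 16 v 16 t test has 80% power for a difference of 1.02 SD.

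**The case against.** The strongest reply is that a different covariate set is defensible here. Hypotheses 1 and 2 are non-randomised, so sex is there to address confounding. Hypothesis 1 cannot adjust for baseline plasticity, which is its outcome, and in Hypothesis 2 plasticity is the predictor. Hypothesis 3 is randomised and adjusts for each participant's own pre-rTMS plasticity, the variable through which the protocol links sex to the outcome. The 95% interval already allows for chance imbalance, and the comparison is openly exploratory. All of this stands. It makes the omission a matter of efficiency and consistency, not an error that invalidates the analysis. It does not remove the remainder, because a baseline that correlates imperfectly with follow-up absorbs only part of a stable sex difference.

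A reader might infer more than the article supports:

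- *That randomisation is unstratified.* The article is silent, and a condensed article commonly leaves strata and block size to the full protocol. The 13.5% is conditional on no stratification by sex. If the blocks are stratified by sex, imbalance largely disappears, and the usual practice of including the stratification factor would still favour sex in the model.
- *That the comparison is biased.* Chance imbalance under randomisation is not systematic bias, as step 4 shows.
- *That an 8 v 3 split moves the result by 0.16 SD.* That gives the baseline covariate no credit for a 0.5 SD sex effect.
- *That the baseline is unusually noisy, or that response to rTMS differs by sex.* The article gives no reliability figure, cites reproducibility of PAS-EEG in independent samples, and speaks only of sex differences in plasticity.

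**Conclusion.** The point holds as a minor one. The stated Hypothesis 3 model omits a recorded factor that the protocol itself relates to the outcome and includes in its other two models. The planned analysis is nonetheless valid: unbiased over randomisations, with nominal type I error.

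The consequence is conditional. If allocation is not stratified by sex and exactly 11 females are enrolled, about one trial in seven would have arms differing by 5 or more females. In those trials the estimate would move by roughly 0.06 to 0.17 SD. This rests on assumed sex effects of 0.5 to 0.8 SD and correlations of 0.3 to 0.6, none of which the article gives. The shift is small beside the differences that 16 per arm can detect, but it is avoidable at almost no cost.

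**What to change.** Before unblinding, prespecify sex as an additional covariate in the Hypothesis 3 ANCOVA, beside arm and pre-rTMS CEA ratio, in line with Hypotheses 1 and 2. Design and setting keeps the investigators blinded until the data analysis is complete, so the addition can be made without sight of results by arm. Adding sex only after an imbalance is seen would be data-driven.

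The cost is one residual degree of freedom (29 to 28) and about 1.5% in the SD of the estimate if sex turns out not to be prognostic beyond baseline. No new data are needed and the randomisation does not have to change.
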